### Data collection and management

To ensure the accuracy and completeness of the study data, the following data collection and management strategies will be employed.(1) Electronic Case Report Form (eCRF Forms): The eCRF forms will serve as the primary data collection tools for this study, containing clear instructions and annotations. They will be designed to include range and format checks for data entry to minimize errors. Data collection and entry will be handled by two members of the research team, who will not be involved in data analysis, and will perform double-checking. Regular quality control checks will be conducted to ensure data integrity and accuracy. Data analysts will use a blinded dataset for analysis, with blinding maintained until the database is locked.(2) Data Isolation and Confidentiality: Records containing participant names or other identifiable information (e.g., informed consent forms and contact information sheets) will be stored separately from the study data records. Study data will be identified only by participant number and initials to protect privacy.(3) Data Access Control: Data will be stored in password-protected computer systems. Only the Principal Investigator (PI) and authorized research team members will have access to files related to personal data, with all access activities recorded to prevent unauthorized access.(4) Database Management: The final database will be managed by the statistician for subsequent statistical analysis. Before analysis, the data management team will clean and anonymize the data to remove any information that might identify participants.(5) Data Monitoring Committee (DMC) Role: The DMC will periodically review the database to ensure data quality and consistency. The DMC will review the database at key study milestones (after enrolling 30%, 50%, 80%, and 100% of participants) to check for missing, suspicious, and inconsistent data. The DMC will also receive interim results and regularly review safety reports to assess the strength of the evidence and the absolute degree and severity of any safety signals.(6) Special Permissions: Access to the database for personal information retrieval requires special permission, which must be granted by the PI and the DMC. Apart from the PI and the statistician, no one else will have access to the database.

### Sample size calculation

Based on previous research data, the incidence of PHN in patients over 50 years old who receive standard antiviral treatment for HZ is 34.8%, while the incidence of PHN after repeated TPVB injections with lidocaine and triamcinolone is 16.3% (Ma et al., 2022). We predict a similar incidence rate in this study, based on the comparable treatment regimen and patient population. Sample size calculation is performed using PASS V.15 software (NCSS, Kaysville, UT, United States) with α = 0.05, β = 0.1, and power = 90%. Considering a dropout rate of 10%, we plan to recruit 127 patients per group, totaling 254 patients, with a 1:1 randomization ratio.

### Handling bias and missing data

Multiple imputation will be used to address missing data. For outliers, the decision to correct, remove, or apply data transformation methods will be based on the source and nature of the outliers to mitigate their impact. We will conduct sensitivity analyses to assess the impact of missing data. Potential sources of bias will be addressed through thorough data monitoring and regular audits by the DMC.

### Statistical analysis

Data analysis will be conducted using R 4.3.0 software. Both intention-to-treat (ITT) and per-protocol (PP) analyses will be performed. The ITT analysis will include all randomized participants, regardless of adherence to the protocol, to avoid bias from excluding participants who may have dropped out or not followed the protocol precisely. The PP analysis will only include participants who completed the study according to the protocol, providing a measure of efficacy under ideal conditions. This dual approach ensures the robustness and generalizability of the results. The statistical methods for primary and secondary outcomes are as follows.

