### Objectives

The primary objective of this trial is to compare the efficacy of DXP combined with ropivacaine versus antiviral treatment alone in preventing ZAP from progressing to PHN within 12 months of follow-up, with the primary evaluation metric being the incidence rate of PHN, defined as a Numeric Rating Scale (NRS-11) score of ≥4 3 months after rash onset.

Secondary objectives include assessing the reduction in pain intensity, improvement in sleep quality (using the Pittsburgh Sleep Quality Index), enhancement of quality of life (using the Short Form Health Survey SF-12), decrease in weekly analgesic consumption, and changes in levels of inflammatory markers (C-Reactive Protein (CRP), Tumor Necrosis Factor-alpha (TNF-α), and Interleukin-6 (IL-6)).

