### Withdrawal criteria

(1) Health Changes: Participants developing additional health issues, complications, or significant physiological changes that render them unsuitable for continued participation will be classified as dropouts.(2) Adverse Events: Participants experiencing serious or critical adverse events, which, upon our research team’s assessment, necessitate discontinuation, will be withdrawn from the study.(3) Protocol Violations: Participants who self-administer non-protocol drugs or undergo external treatments will be considered in breach of the protocol and will be excluded.(4) Voluntary Withdrawal: Participants may opt to withdraw for personal reasons or may be lost to follow-up during the concluding phase of the study.

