#### Study outcomes

The baseline demographics characteristics of the patients will be collected through searches of the institution’s electronic medical records or direct questioning of the participants. Data collected from the electronic medical records will include gender, age, BMI affected nerves, average weekly consumption of analgesics and levels of inflammatory markers. Data obtained directly from the patients will include pain scores (NRS-11 scores), the Pittsburgh Sleep Quality Index (PSQI), quality of life score, and pain characteristics for comparison with post-intervention outcomes. All patients will undergo systematic follow-up after receiving treatment. The follow-up schedule, outlined in Table 1, is designed to comprehensively assess the long-term outcomes of the treatment. Patients will be followed up at 1, 3, 6, and 12 months post-treatment. These time points were selected based on the natural course of herpes zoster-associated pain and the development of PHN. PHN is typically defined as pain persisting beyond 3 months after the onset of the rash, hence the inclusion of the 3-month mark as a primary time point for assessing PHN incidence (Ahronowitz and Fox, 2018; Ma et al., 2022; Rowbotham and Petersen, 2001). The 1-month and 6-month follow-ups allow for the assessment of intermediate outcomes, such as pain intensity, sleep quality, and inflammatory markers, while the 12-month follow-up provides data on the long-term efficacy and safety of the intervention. The follow-up assessments include the following.

**TABLE 1 T1:** Time schedule of participant enrolment, allocation and assessment.

	Enrolment	Allocation	Post-allocation											Close out
Time point	D0	D0	D1	D2	D3	D4	D5	D6	D7	D14	M1	M3	M6	M12
Enrolment														
Eligibility screening	√													
Informed consent	√													
Allocation		√												
Intervention														
Antiviral therapy			√	√	√	√	√	√	√					
Thoracic Paravertebral Nerve Block Treatment			√							*				
Assessment														
Demographics	√													
Incidence rate of PHN												√	√	√
NRS-11	√	√	√	√	√	√	√	√	√	√	√	√	√	√
Skin lesions	√	√	√	√	√	√	√	√	√	√	√	√	√	√
Pain characteristics and	√	√	√	√	√	√	√	√	√	√	√	√	√	√
SF-12		√							√			√	√	√
PSQI		√							√			√	√	√
Levels of inflammatory markers		√							√			√	√	√
Consumption of analgesics			√	√	√	√	√	√	√	√	√	√	√	√
Adverse events			√	√	√	√	√	√	√	√	√	√	√	√

*If NRS-11 ≥ 4 at D14, a second TPVB, injection may be performed.

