#### Primary outcome

Incidence Rate of PHN: PHN is defined as a condition characterized by pain in the dermatomal area that persists for a duration exceeding 3 months following the resolution of the herpetic rash (Kost and Straus, 1996). The incidence rate of PHN will be precisely determined by assessing the percentage of patients who exhibit an NRS-11 score ≥4 during scheduled follow-up visits at 3, 6, and 12 months (patient-reported).

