### Comprehensive evaluation

The study’s design, which includes both immediate and follow-up assessments, allows for a comprehensive evaluation of both short-term and long-term outcomes. The primary outcome is the incidence rate of PHN, defined as an NRS-11 score of ≥4 3 months after rash onset. Secondary outcomes include reductions in pain intensity, improvements in sleep quality (using the Pittsburgh Sleep Quality Index), enhancements in quality of life (using the SF-12), decreases in weekly analgesic consumption, and changes in levels of inflammatory markers (CRP, TNF-α, IL-6). If successful, this study could provide a new, effective treatment option for managing ZAP and preventing PHN, significantly improving patient outcomes.

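### The per-protocol set is tied to completing a study that closes at month 12, so events after month 3 can remove patients from the per-protocol analysis of the 3-month PHN rate

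*Protocol article*

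**What the plan says.** **Analysis sets.** The Statistical analysis section plans both ITT and PP analyses. ITT takes everyone randomised, whatever their adherence. For PP: "The PP analysis will only include participants who completed the study according to the protocol, providing a measure of efficacy under ideal conditions". No visit or cut-off is attached to completion. The section does not say which analysis is primary, and it presents the pair as what makes the results robust.

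**Follow-up.** Under Study outcomes: "Patients will be followed up at 1, 3, 6, and 12 months post-treatment". Table 1 heads the month-12 column as close-out.

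**Primary time point.** Objectives gives the primary metric as PHN incidence, "defined as a Numeric Rating Scale (NRS-11) score of ≥4 3 months after rash onset". Comprehensive evaluation repeats it: "The primary outcome is the incidence rate of PHN, defined as an NRS-11 score of ≥4 3 months after rash onset". Study outcomes explains the schedule with "hence the inclusion of the 3-month mark as a primary time point for assessing PHN incidence". Other places go further. The Primary outcome section counts "patients who exhibit an NRS-11 score ≥4 during scheduled follow-up visits at 3, 6, and 12 months", Table 1 ticks PHN incidence at M3, M6 and M12, and Objectives also frames the aim as success "in preventing ZAP from progressing to PHN within 12 months of follow-up".

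**Leaving the study.** Withdrawal criteria, item 3, excludes participants who take non-protocol drugs or have outside treatment, with no time limit. Item 4 covers those who withdraw for personal reasons or "may be lost to follow-up during the concluding phase of the study".

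**The concern.** A PP analysis of a 3-month endpoint should ask what happened to patients who followed the protocol up to month 3. If the set requires completion to month 12, it also asks what patients did in the nine months after the endpoint was recorded. Those later events are not neutral. A patient who still has PHN at month 3 has a reason to seek outside treatment and so breach the protocol. A patient who is free of pain has less reason to keep attending. Because the trial is open-label for patients, both tendencies can differ by arm.

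The PP set could then be selected partly on the outcome it is meant to estimate. PP could disagree with ITT, or appear to confirm it, for reasons unrelated to efficacy under adherence. That matters because the plan does not rank the two analyses and relies on having both as evidence of robustness. Month-3 results already collected would also be left out of the PP analysis.

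**Working it through.** **1. Reading the rule.** The PP sentence names no month. Month 12 is inferred from the follow-up schedule and the close-out column of Table 1; the article gives no other completion point. Take a patient treated as assigned, with an NRS-11 recorded at M3, who is lost at month 8 or starts outside treatment at month 5. Under Objectives and Comprehensive evaluation, this patient's primary outcome is known. Under the PP sentence, the patient did not complete the study according to the protocol and is out.

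**2. The plan's own figure.** Inputs from Sample size calculation: p1 = 0.348 (control), p2 = 0.163 (intervention), α = 0.05 (taken as two-sided), power 90%, dropout 10%.

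n = [1.960·√(2·p̄(1−p̄)) + 1.282·√(p1(1−p1) + p2(1−p2))]² / (p1−p2)², with p̄ = 0.2555

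= (1.209 + 0.772)² / 0.185² = 114.7, so 115 per group.

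With 10% dropout this is 115 × 1.1 = 126.5, so 127, or 115/0.9 = 127.8, so 128. The stated 127 per group reproduces. Power at the planning rates is 92.7% with 127 per group and 89.9% with 127 × 0.9 = 114.3 per group.

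**3. Effect of late removals on the PP estimate.** Let f be the share of M3 PHN cases, and g the share of non-cases, removed between M3 and M12. In each arm:

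PP rate = p(1−f) / [p(1−f) + (1−p)(1−g)]

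Example, control with f = 0.30 and g = 0.05: 0.2436 / (0.2436 + 0.6194) = 28.2%. Intervention with f = 0.10 and g = 0.05: 0.1467 / (0.1467 + 0.79515) = 15.6%. RR = 0.552.

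The document gives no values for f or g. All shares below are assumptions. C = control, I = intervention; g is the same in both arms.

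| f (C / I) | g | Arm removed (C / I) | PP rate C vs I | Difference (points) | RR |
|---|---|---|---|---|---|
| none | none | 0 / 0 | 34.8% vs 16.3% | 18.5 | 0.468 |
| 10% / 10% | 10% | 10% / 10% | 34.8% vs 16.3% | 18.5 | 0.468 |
| 0 / 0 | 10% | 6.5% / 8.4% | 37.2% vs 17.8% | 19.4 | 0.48 |
| 5% / 5% | 10% | 8.3% / 9.2% | 36.0% vs 17.1% | 19.0 | 0.47 |
| 30% / 30% | 5% | 13.7% / 9.1% | 28.2% vs 12.5% | 15.7 | 0.445 |
| 30% / 10% | 5% | 13.7% / 5.8% | 28.2% vs 15.6% | 12.7 | 0.552 |
| 10% / 30% | 5% | 6.7% / 9.1% | 33.6% vs 12.5% | 21.0 | 0.374 |

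For scale, the standard error of the difference with 127 per group is √(0.3633/127) = 5.3 points. Loss unrelated to PHN leaves the RR alone and costs only power. Loss mainly of non-cases barely moves the RR. Loss of cases that differs by arm moves it appreciably, in either direction.

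**The case against.** **The primary endpoint may not be month 3 alone.** A reader might infer that the document fixes it there and that the PP rule therefore contradicts it outright. The text does not support that: the Primary outcome section, Table 1 and the 12-month phrase in Objectives all extend PHN beyond month 3, and Study outcomes calls month 3 a primary time point, not the only one. This objection stands against calling the endpoint settled. It does not rescue the rule. No section defines an outcome that needs every visit through month 12, and a set of 12-month completers is still the wrong base for the 3-month and 6-month rates.

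**The wording is shorthand.** A condensed article often leaves PP details to an analysis plan, and month 12 is inferred. That is fair, and the authors may intend a visit-specific set. But the article does state a membership rule, and its natural reading is completion to close-out.

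**The main result is safe.** A reader might infer that the trial's conclusion is biased. It is not shown to be: ITT keeps all randomised patients, and multiple imputation and sensitivity analyses for missing data are planned. The harm is confined to PP. Lost PP power also carries little weight, since the sample size is not stated to be for the PP set.

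**The size is unknown.** A reader might infer a large attenuation. For example, removing 30% of control cases, 10% of intervention cases and no non-cases gives 27.2% vs 14.9%, a difference of 12.3 points and power of about 65%. That scenario assumes one-sided loss of cases and removes 0.348 × 0.30 = 10.4% of controls after M3 alone, more than the plan's whole 10% dropout allowance for that arm. Other equally arbitrary shares give almost no shift, or a shift the other way.

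**Late, outcome-driven loss is not documented.** Withdrawal item 4 names a category; it does not forecast a rate or say that the concluding phase starts after M3. The Interventions section also gives all patients with persisting pain access to standard pain management, which weakens the motive to go outside. Both points stand, so the mechanism is plausible rather than shown.

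**Conclusion.** The point holds in a limited form. Read literally, the PP rule lets losses and breaches after month 3 remove patients whose 3-month result is known, so PP membership can depend on the outcome. This rests on two readings: that completing the study means reaching the month-12 close-out, and that month 3 is a primary time point in its own right.

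The document fixes neither the size nor the direction of the bias. Under the assumed losses in the table, the PP RR lies between about 0.37 and 0.55 against a planning value of 0.47. With 10% loss unrelated to PHN there is no bias and about 90% power. The upper end of that range needs 13.7% of controls removed after M3, so it illustrates a possibility and is not a forecast.

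The analysis should be corrected because PP is unranked against ITT and is offered as support for robustness. It does not threaten the ITT result.

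**What to change.** Make two changes in one edit.

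1. State a single primary time point for PHN, and bring Objectives, Primary outcome, Table 1 and Comprehensive evaluation into line with it. PHN at the remaining visits can then be labelled secondary.
2. Replace the completion rule with a visit-specific PP set: assigned treatment received, no major deviation up to that visit, and an NRS-11 recorded at that visit. Say explicitly that losses and deviations after month 3 do not remove a patient from the PP analysis of the 3-month endpoint. Completion to month 6 or month 12 is then required only for PP analyses at those visits.

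This definition works whichever time point is chosen. It needs no extra patients, visits or data. The small downside is that the PP set differs in size between visits, so the number in each arm has to be reported for each one.

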### Primary outcome

The incidence rate of PHN between the two groups will be compared using the chi-square test. Relative risk (RR) and its 95% confidence interval will be calculated to evaluate the relative risk and effect of DXP with ropivacaine compared to antiviral treatment alone. Although randomization should control for most confounding factors, potential confounding factors such as sex age, baseline pain intensity, and comorbidities will be considered and controlled using multivariate logistic regression analysis.We will assess multicollinearity and select the most relevant predictors using methods like stepwise regression.

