## Introduction

In adults, the reactivation of varicella-zoster virus (VZV), which lies dormant in the dorsal root or trigeminal ganglia, typically results in herpes zoster (HZ). This condition is more common in individuals over the age of 50 (Sun et al., 2021; Cohen, 2013). Due to the neural damage and acute neuritis caused by VZV, patients experience persistent and severe pain, referred to as herpes zoster-associated pain (ZAP), which can become severe during the acute phase of the disease and often progresses to postherpetic neuralgia (PHN) if it persists beyond 90 days, posing significant treatment challenges (Ahronowitz and Fox, 2018; Ma et al., 2022; Rowbotham and Petersen, 2001).

Despite the widespread use of antiviral agents, anticonvulsants, antidepressants, and opioid analgesics, a subset of patients may still require additional therapeutic interventions to achieve adequate symptom control (Patil et al., 2022). This is particularly pertinent for individuals presenting with higher initial pain scores, advanced age, or comorbid conditions, as they remain at an elevated risk for developing PHN (Hashizume et al., 2022; Zhou et al., 2021; Wang et al., 2019). PHN significantly impacts patients' daily lives, leading to anxiety, depression, and sleep disturbances, making the prevention of PHN crucial for HZ patients (Wang et al., 2019). The side effects of medications, such as dizziness and drowsiness from gabapentin or pregabalin, and gastrointestinal issues from opioids, further complicate management strategies (Wang et al., 2023). Therefore, it is essential to minimize ZAP and prevent the occurrence of PHN.

Neuropathic pain is characterized by alterations in ion channels, activation of immune cells, and the involvement of neuroglial mediators. Among the commonly used medications, sodium channel blockers play a crucial role in managing this condition (Wang et al., 2021a). Ropivacaine, a potent sodium channel blocker, achieves its analgesic effect by reversibly inhibiting sodium ion influx, thereby blocking nerve impulse conduction. It is noted for its prolonged duration of action compared to lidocaine and is widely recognized for its safety due to its lipophilic properties, which confer reduced toxicity to both the cardiovascular and central nervous systems (Kaufman et al., 2005). A 0.2% concentration of ropivacaine is effective in providing analgesia with minimal motor impairment, making it suitable for epidural analgesia (Dresner et al., 2000).

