### Inclusion criteria

(1) Age ≥50 years with a diagnosis of thoracic HZ.(2) Disease duration ≤2 weeks.(3) Baseline pain intensity with an NRS-11 ≥ 4 points (Baseline pain intensity is the mean pain intensity score within 24 h before randomization).(4) Patients experiencing a first episode of HZ who have not received any other interventions.

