### Randomization and blinding

#### Randomization method

Participants will be randomly assigned in a 1:1 ratio to receive either antiviral treatment combined with DXP and ropivacaine or antiviral treatment alone, using a computer-generated random sequence created with IBM SPSS Statistics 25.0. The sequence will be stored in numbered opaque envelopes to ensure allocation concealment. The efficacy and safety assessments will be conducted by independent evaluators who are blinded to the group assignments.

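### The primary chi-square test and crude relative risk are valid but leave out baseline NRS-11 and age, so the declared effect measure is never adjusted and a modest amount of precision is given up

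*Protocol article*

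**What the plan says.** In the protocol article, the Primary outcome paragraph under Statistical analysis sets out three things:

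- The test: "The incidence rate of PHN between the two groups will be compared using the chi-square test".
- The effect measure: "Relative risk (RR) and its 95% confidence interval will be calculated". No covariates are mentioned for it.
- A further model, in which sex, age, "baseline pain intensity, and comorbidities will be considered and controlled using multivariate logistic regression analysis". The authors will also "select the most relevant predictors using methods like stepwise regression".

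The paragraph does not say how this model ranks against the chi-square test.

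Elsewhere, the Introduction singles out "individuals presenting with higher initial pain scores, advanced age, or comorbid conditions, as they remain at an elevated risk for developing PHN". Inclusion criterion 3 requires NRS-11 of at least 4 at entry and specifies that "Baseline pain intensity is the mean pain intensity score within 24 h before randomization", so every randomised patient has a baseline value on the scale that defines the outcome. Age is an eligibility criterion (50 years or older) and is listed among the baseline data. The Randomization method section describes allocation "using a computer-generated random sequence created with IBM SPSS Statistics 25.0" and mentions no stratification by baseline pain or age.

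**The concern.** The outcome is a threshold on NRS-11, and the same scale is measured before randomisation in everyone. The protocol thus identifies two prognostic variables, collects both on all patients, and leaves both out of the test and the effect measure on which the trial will be read.

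The planned regression does not repair this as written. It is presented as a guard against confounding and its covariates are chosen from the data. Its treatment effect is a conditional odds ratio, while the declared measure is the RR. With PHN this common the two scales are far apart, so the regression cannot stand in for an adjusted RR. At stake are a somewhat wider confidence interval and somewhat lower power than the collected data allow, and an adjusted result on a different scale from the headline.

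**Working it through.** **Inputs from the protocol.** PHN 34.8% (control) and 16.3% (intervention), α = 0.05, power 90%, 10% dropout, 127 per group (Sample size calculation). Sidedness is not stated; two-sided reproduces the plan's number.

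**Step 1: the plan's own figure.** Two-proportion formula, pooled variance under the null, no continuity correction:

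n = [1.960·√(2·p̄·(1−p̄)) + 1.282·√(p₁(1−p₁) + p₂(1−p₂))]² / (p₁−p₂)²

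- p̄ = (0.348 + 0.163)/2 = 0.2555, so the first root is √0.3804 = 0.6168.
- The second root is √(0.2269 + 0.1364) = 0.6028.
- p₁ − p₂ = 0.185.
- n = (1.2089 + 0.7725)²/0.0342 = 114.7, so 115 per arm.
- Dropout: 115/0.9 gives 128, and 115 × 1.1 gives 127.

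The stated 127 is reproduced, and it corresponds to the unadjusted comparison.

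**Step 2: power of the chi-square test.** 127 × 0.9 = 114 evaluable per arm. Then (0.185·√114 − 1.2089)/0.6028 = 1.271, which gives 89.8%. If all 127 are evaluable, power is 92.7%.

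**Step 3: the two scales.**

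- RR = 0.163/0.348 = 0.47.
- OR = (0.163/0.837)/(0.348/0.652) = 0.1947/0.5337 = 0.36.

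This OR is the marginal one. With prognostic covariates in the model, the conditional OR lies further from 1.

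**Step 4: what adjustment would add.** The protocol gives no prognostic strength, so a range is assumed: one standard-normal score combining baseline pain and age, with an OR of 1 to 3 per standard deviation (SD). Each scenario had 5,000 simulated trials with 114 per arm. The chi-square test was compared with a logistic model standardised to a marginal risk difference. Needed n is 115 divided by the variance ratio.

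| Assumed OR per SD | Chi-square power | Adjusted power | Gain (points) | Variance ratio, unadjusted/adjusted | Evaluable n per arm for 90% |
|---|---|---|---|---|---|
| 1.0 | 90.5% | 90.6% | 0.1 | 1.00 | 115 |
| 1.5 | 89.7% | 90.7% | 1.0 | 1.03 | 112 |
| 2.0 | 90.6% | 92.5% | 1.9 | 1.07 | 108 |
| 2.5 | 89.2% | 92.8% | 3.6 | 1.13 | 102 |
| 3.0 | 89.4% | 93.9% | 4.5 | 1.19 | 97 |

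A ratio of 1.03 to 1.19 means the variance falls by about 3% to 16% (1 − 1/1.03 to 1 − 1/1.19). Simulation error on each power is about 0.4 points (√(0.9 × 0.1/5000)). Type I error of the adjusted estimate was 4.9% to 5.6%. A separate simulation testing the standardised log RR over OR 1.5 to 3 gave a gain of about 0 to 4 points, with type I error at or below 5%. Together these give the range of roughly 0 to 4.5 points.

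**Step 5: if the two analyses stayed unranked.** Under no effect (4,000 runs, 114 per arm, fixed covariates), the chi-square and the adjusted model disagreed in 2.1%, 2.8% and 3.8% of trials for OR per SD of 1.5, 2 and 3. Claiming success on either gave a type I error of 5.7%, 6.4% and 6.9%. Stepwise selection was not simulated.

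**The case against.** A chi-square test with a crude RR is a standard, valid analysis of a 1:1 randomised binary outcome. It is the analysis the sample size was built on, and it has about 90% power without any adjustment. Adjustment for age and baseline pain is also already planned in the same paragraph. All of this stands, and it limits the point to efficiency and to the scale of the adjusted result.

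Three stronger readings are tempting, and the document does not support them:

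- **That chance imbalance in baseline pain or age biases the RR.** Under randomisation the unadjusted test and interval already allow for such imbalance, and type I error stays at 5%. The lack of described stratification does not change this, and an article may condense randomisation detail.
- **That the gain exceeds 6 points.** Scaling the variance by 1 − ρ² with ρ = 0.5 gives 96.2% power, against 89.8%. That correlation needs an OR of about 4.5 per SD, which nothing in the protocol supports. The entry floors for NRS-11 and age narrow both covariates and point to the low end of the range.
- **That the plan inflates type I error.** Step 5 applies only if success could be claimed on either analysis. The chi-square and RR come first and match the sample size, and the regression is worded as supportive, so the natural reading is that the chi-square decides. A formal ranking may also be left to an analysis plan that is not shown.

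The objection does not remove the main fact: as written, the declared RR is never adjusted, and the one adjusted analysis is on another scale with data-selected covariates.

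**Conclusion.** The point holds as a modest, inexpensive improvement in precision and does not challenge validity. The chi-square has 89.8% power at 114 evaluable per arm. Prespecified adjustment would add roughly 0 to 4.5 points for an assumed OR per SD of 1.5 to 3, and essentially nothing if the covariates turn out not to be prognostic. The size rests wholly on that assumed range. What does not depend on it is the mismatch of scales: RR 0.47 against OR 0.36 at the planned rates, with no adjusted version of the measure the protocol reports. The type I error of about 5.7% to 7% is conditional on leaving the two analyses unranked and accepting either, which the protocol does not say it will do.

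**What to change.** Reword the Primary outcome paragraph under Statistical analysis as follows:

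- **Model.** Logistic regression of PHN on treatment, baseline NRS-11 and age, both continuous and fixed in advance, without stepwise selection. If sex or comorbidities are to be kept, define them and fix them in the list beforehand too.
- **Estimate.** Standardise the model over all randomised patients to a marginal RR and risk difference, each with a 95% confidence interval, and carry out one two-sided 5% test.
- **Time point.** Tie that test to one named visit. The Objectives refer to 3 months after rash onset, whereas the outcome definition counts visits at 3, 6 and 12 months, so the primary visit has to be stated.
- **Missing data.** Compute the standardised estimate within each imputed dataset and pool, in line with the multiple imputation already planned.
- **Ranking.** State that this analysis decides the trial, and keep the chi-square test and crude RR as supporting.

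The cost is a revised paragraph and a few lines of R. The sample size, the data collected and the reported effect measure stay as they are. The downside is a slightly less simple headline analysis.
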